**Figure 2. f2:**
[figure not shown]
Study 2 design overview.

Three research questions and two hypotheses are therefore set for Study 2:
•Research Question 1: Does the Cox Survival Analysis model derived in Study 1 replicate amongst
*N* = 25 BD participants in an LMIC cohort?•Research Question 2: Does Dynamic Bayesian Network Analysis enable examination of relapse prediction amongst
*N* = 25 BD participants in an LMIC cohort?•Research Question 3: Does Hadaeghi’s Complex System Model of relapse prediction derived in Study 1 replicate amongst
*N* = 25 BD participants in an LMIC cohort?•Hypothesis 1: Amongst the complete sample (
*N* = 50), Relative Amplitude will correlate with the diurnal amplitude of both circadian gene expression and blood metabolites.•Hypothesis 2: Diurnal amplitude of circadian gene expression and blood metabolites, and Relative Amplitude will be attenuated in people with interepisode BD (
*N* = 25) compared to age, gender, and employment-matched healthy controls (
*N* = 25).

*Study 3: Exploring generalisability of the Complex System model of state transition from relapse prediction to treatment response.*

Study 3 contributes to the project’s secondary mechanistic aim by investigating if complex system features found in Study 1 to predict relapse (state transition into an episode) generalise to prediction of treatment response from an acute episode (state transition to recovery). If generalisation is demonstrated, it could be hypothesised that Hadaeghi’s Complex System Model captures generic system instability (as opposed to a relapse-specific process).

The primary aim of Study 3 is therefore to investigate whether the relapse risk algorithm informed by Hadaeghi’s Complex System Model (trained and tested on Study 1 data) can be extended to response to treatment.
^
19
^ The state transition of Study 3 is measured in binary response to treatment. Response to treatment at 8 weeks is operationalised as 50% reduction in MADRS (for those in depressive episode at baseline) or 50% reduction in YMRS (for those in manic episode at baseline). Participants will wear actigraphs for 21 days – for consistency with Study 1 and 2, the first 14 days only will be used in modelling of binary response to treatment.
Figure 3 below summarises the study design for this primary aim.

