*symptom burden* in the follow-up window (three epochs in Study 1, one in Study 2). Weekly symptom burden will be measured on the LIFE on 6-point scales for weekly depression and mania (see above). Second, in all studies, modelling analyses will be re-conducted using the outcome measure of self-reported Quality of Life (QoL), a patient-valued outcome. For the present project, QoL scores have the advantage of being a meaningful variable in both the interepisode cohorts of Study 1 and 2, and the highly symptomatic cohort of Study 3. The BD-specific QoL.BD [short form,
83,
84] will be collected at 13-
and 26-week follow-ups in Study 1 and 2 and at the week 8 endpoint in Study 3.

*Study 3: Treatment response*

The primary outcome variable in Study 3 will be 50% reduction in MADRS or YMRS scores at 8 weeks. The prospective relationship between weekly RAR and weekly symptom assessments (MADRS, YMRS, CGI) for 21 days will be explored to investigate dynamics of RAR in relation to symptoms over these shorter timeframes.

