The extracted indicators will include statistical, time–frequency, and nonlinear features derived from the activity time series and computed over sliding temporal windows, yielding time-varying feature trajectories that reflect changes in system stability. Statistical features (e.g., mean, variance, skewness) will describe overall activity levels; time–frequency features (e.g., spectral power, rhythm amplitude, phase stability) will capture periodicity and circadian patterns; and nonlinear features (e.g., sample entropy, fractal dimension, Lyapunov exponent, correlation dimension, detrended fluctuation analysis) will quantify the complexity and predictability of rest–activity dynamics.

The predictive framework will be implemented using nonlinear dynamic modelling approaches, such as recurrent neural networks (RNNs) or nonlinear autoregressive models, which model sequences of time-indexed feature vectors and are, therefore, well-suited to capturing feedback relationships and temporal dependencies in evolving system dynamics. These models do not explicitly recover the underlying dynamical equations but are designed to learn temporal dependencies in the observed data. These data-driven models are conceptually aligned with Hadaeghi’s formulation of BD as an interacting dynamical system.

The model will be trained to identify patterns and trajectories in these features that precede critical transitions in system stability. In Studies 1 and 2, these transitions will correspond to relapse events among interepisode participants, while in Study 3 they will represent treatment response during acute manic or depressive episodes.

*Input and outcome variables for modelling*

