The primary input data for all predictive modelling in Studies 1, 2 and 3 will consist of 14 days actigraphy time-series and derived features extracted through both time-domain and frequency-domain analyses. Feature extraction will include conventional RAR metrics such as the Van Someren variables (Relative Amplitude, Intradaily Variability, and Interdaily Stability), sleep–wake regularity, rhythm phase, and fragmentation, as well as signal-based features obtained from Fourier and wavelet analyses that capture periodicity, spectral power distribution, and nonstationary temporal patterns. Together, these actigraphy-derived metrics will form the principal set of predictors for analyses based on Cox Survival Analysis, Dynamic Bayesian Networks, Hadaeghi’s Complex System Model of BD and other machine learning approaches to be explored.

Auxiliary variables, including demographic and clinical data, will be used to support feature interpretation and to define model outcomes. In Studies 1 and 2, the primary outcome will be relapse, defined as the onset of a new depressive, manic or hypomanic episode meeting DSM-5 diagnostic criteria. Relapse will be identified through structured follow-up interviews using the LIFE (above). Time to first relapse will also be analysed as a survival outcome. In Study 3, the primary outcome will be treatment response, defined as at least a 50% reduction in baseline MADRS or YMRS scores at 8-week endpoint.

These outcome variables will be used to label actigraphy epochs and to train, validate, and compare predictive models of relapse risk and treatment response.

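### Study 3 says its features precede treatment response, but the 14-day predictor window can include the response itself, so full-sample accuracy would not by itself show forecasting

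*Protocol article*

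**What the plan says.** Section 2.6 (Hadaeghi's Complex System Model) describes what the model is to learn: "The model will be trained to identify patterns and trajectories in these features that precede critical transitions in system stability". It then says what the transitions are: relapse in Studies 1 and 2, whereas "in Study 3 they will represent treatment response during acute manic or depressive episodes".

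Section 2.2 (Study 3) fixes the outcome: "The state transition of Study 3 is measured in binary response to treatment", and "Response to treatment at 8 weeks is operationalised as 50% reduction in MADRS", or in YMRS for manic patients. Section 2.6 (Input and outcome variables) repeats it as "defined as at least a 50% reduction in baseline MADRS or YMRS scores at 8-week endpoint" and adds: "These outcome variables will be used to label actigraphy epochs".

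The predictor window is also fixed. Patients wear the device for 21 days from baseline, but "the first 14 days only will be used in modelling of binary response to treatment". Section 2.7 (Risk management Study 3) puts every participant under active specialist care, so treatment runs during the recording.

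Weekly ratings are planned over the same period. Section 2.4 says: "The prospective relationship between weekly RAR and weekly symptom assessments (MADRS, YMRS, CGI) for 21 days will be explored". Section 2.2 assigns this work to a tertiary, exploratory aim.

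**The concern.** A feature can precede a transition only if the transition comes after the recording. The Study 3 definitions do not ensure this. Patients enter in a severe episode under treatment, so some may reach a 50% fall within the 14 days. If they hold it to week 8 they are positive cases, and the later part of their actigraphy comes from someone who has already met the response criterion. Nothing in the article identifies or separates them.

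This bears on the interpretation the study is built for. Section 2.2 proposes that, if features that forecast relapse also predict recovery, the model may be capturing instability in general rather than a relapse-specific process. Research Questions 1 and 2 pool Study 1 and Study 3 samples into one state-transition model. A model that partly recognises patients who are already better could appear to generalise without forecasting anything in them.

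**Working it through.** **Figures available.** The power analysis in section 2.6 covers Study 1 only. For Study 3 the article gives no response rate, time course, accuracy target or power, so there is no stated figure to reproduce.

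**Timing check.**

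- Predictor: days 1-14 (section 2.2).
- Label: one status at week 8 (day 56), relative to baseline (sections 2.2, 2.4, 2.6).
- Claim: features precede the transition, which is treatment response (section 2.6).
- A 50% fall on or before day 14, held to day 56, gives a positive label, although some of the predictor series follows the fall. The claim fails for that patient.
- A first 50% fall after day 14, present at day 56, gives a positive label and satisfies the claim.

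The label does not distinguish these two patients. This follows from the definitions alone.

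**Illustrative size (assumptions, not figures from the article).** Assume a constant response hazard h from day 0, response once reached is kept, and a week-8 response proportion p of 0.4 to 0.8. Then h = -ln(1 - p)/56, and:

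- share of responders across by day 14 = (1 - exp(-14h))/(1 - exp(-56h)) = (1 - (1 - p)^(1/4))/p
- patients across by day 14 = 45 × (1 - (1 - p)^(1/4))
- day-14 landmark set = 45 minus that number

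| p | (1 - p)^(1/4) | Share of responders across by day 14 | Patients across, of 45 | Landmark set |
|---|---|---|---|---|
| 0.4 | 0.880 | 0.30 | 5.4 | 39.6 |
| 0.5 | 0.841 | 0.32 | 7.2 | 37.8 |
| 0.6 | 0.795 | 0.34 | 9.2 | 35.8 |
| 0.7 | 0.740 | 0.37 | 11.7 | 33.3 |
| 0.8 | 0.669 | 0.41 | 14.9 | 30.1 |

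This gives about 5 to 15 patients already across and about 30 to 40 in the landmark set. Delayed onset of response lowers the first range and front-loaded response raises it. One hazard is applied to both polarities, although section 2.6 says recovery is less likely from depressive episodes.

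**Wider range without the hazard assumption.** Let s be the share of week-8 responders already across by day 14. With p from 0.4 to 0.7 and s from 10% to 50%, the number is 45 × p × s, from 45 × 0.4 × 0.1 = 1.8 to 45 × 0.7 × 0.5 = 15.8, or about 2 to 16 patients.

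**What this could do to apparent accuracy (illustration).** Take a feature that reads only whether the patient has already crossed by day 14. Let f be the share of week-8 non-responders who crossed by day 14 and lost it. For such a binary feature, AUC = 0.5 + 0.5 × (s - f).

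- f = 0: s = 10%, 20%, 30%, 50% gives AUC 0.55, 0.60, 0.65, 0.75.
- f = 10%: the same values of s give 0.50, 0.55, 0.60, 0.70.

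This feature has no forecasting content. Lost responses partly offset the effect, so its net size is uncertain.

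**The case against.** Response status at week 8 is a legitimate endpoint for predicting treatment result, and the article calls that an important clinical question. The project describes itself as exploratory, a detailed analysis plan and study-level protocols are still to come, and a landmark analysis is the sort of item such a plan could hold. The sizes above rest wholly on assumptions. All of this stands, and it limits the point to interpretation. It does not remove the point, because the window, the label and the claim that features precede the transition are already fixed in this article and do not fit together for early responders. The planned 21-day exploration of actigraphy and ratings is not tied to the primary label.

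Three stronger readings are tempting and not supported:

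- *The protocol dates every transition at week 8.* It does not. It reads a status at week 8 and gives no date.
- *A patient who falls 50% early and loses it by week 8 is mislabelled.* Under the stated definition that patient is a non-responder. Whether a reversed fall counts as a shift to a new state is interpretation, and nothing in the article gives its frequency.
- *The full-sample analysis should be replaced by a landmark analysis.* Research Questions 1 and 2 already split 45 patients into x for retraining and 45 - x for testing, and Research Question 3 has only 15 manic patients. Shrinking the main analysis set would strain all three.

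**Conclusion.** The point holds as a limit on inference. For patients who reach a 50% fall by day 14 and keep it, the features do not wholly precede the transition, and the plan does not separate these patients. Full-sample accuracy could therefore be partly concurrent detection, and would not by itself support forecasting of recovery or a general-instability mechanism.

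The number affected cannot be known from the document. About 5 to 15 of 45 is an illustration under a constant hazard, sustained response and 40-80% response at week 8; the looser assumptions give about 2 to 16. The AUC values show only that the effect could be material. The week-8 outcome itself is not at fault.

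**What to change.** Keep week-8 response in all 45 patients as the primary outcome and as the Research Question 1-2 analysis. Then:

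1. Pre-specify a day-14 landmark analysis restricted to participants who have not reached a 50% fall in MADRS or YMRS, as applicable, at the week-2 rating. This takes the planned weekly ratings to include one at about day 14.
2. State that the forecasting or generalisation interpretation depends on the landmark result.
3. Report participants already across by day 14 separately, as concurrent detection.
4. Optionally, report descriptively how many were across by day 21 but were not responders at week 8. No ratings are described between day 21 and week 8, so later reversals cannot be dated.

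The cost is wording in the forthcoming analysis plan and one further analysis of ratings already planned. The landmark set would be about 30-40 patients under the assumptions above, with wider intervals. It reduces concurrent detection but does not remove it: a patient with a 45% fall at day 14 stays in the set, and that patient's actigraphy may already reflect improvement. The report should say so.

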### Procedures

2.7

*Project registration*

The three-study project as detailed here was registered with Open Science Foundation on 24
^th^ April 2025 (
https://doi.org/10.17605/OSF.IO/UABNJ).

*Ethics*

All three studies have ethics approval. Ethics approval for Study 1 was provided by Swinburne University of Technology Human Research Ethics Committee (SUHREC/2025/8127). Study 2 has received biosafety approval from Institutional Biosafety Committee (IBSC) of Indian Institute of Technology Hyderabad and Institutional Ethics Committees of the Medical College Kolkata and Indian Institute of Technology Hyderabad (ITH/IEC/2025/01/2). Study 3 received approval from the New Zealand Health and Disability Ethics Committee (HDEC, 2024 EXP 22105). Scientific findings will be reported according to the Strengthening the Reporting of OBservational studies in Epidemiology (STROBE) guidelines.
^
104
^ The project sponsor is Swinburne University of Technology.

*Risk management approach Study 1 and Study 2*

In all studies, treatment as usual continues throughout. Risk management for Study 1 and 2 has been developed through our experience with other online interventions and websites for BD [e.g.,
105–
108], and through consultation with our lived experience colleagues. Key principles of the approach include protection of autonomy where possible, explicit assignment of risk management to participants and their local networks, and advance planning for crises.
^
109
^ Statements of informed consent highlight, (i) the project cannot and does not provide any therapy, treatment, support, or emergency management, (ii) the participant and their local networks of care remain central in their own safety and well-being throughout. The project landing page reiterates that no crisis support can be obtained through the site, but includes a ‘crisis’ tab, which provides suicide hotline phone numbers worldwide (

*unsuicide.wikispaces.com*
).

To minimise the impact of any adverse events in Study 1 and 2, being under the ongoing care of a nominated medical practitioner is an inclusion criterion. In Study 1, once participants consent, an email will be sent to their practitioner noting that the patient has enrolled in the study, that the researchers are not taking over their care, and that the provider will potentially be contacted should the researchers become aware of crisis or risk. At each follow-up assessment interview, clinicians’ contact details will be updated if required and suicidality checked by re-administering the CSSRS.

Four specific risk management processes of Studies 1 and 2 are noteworthy. First, active suicidality (operationalised as CSSRS of 3, 4 or 5) is an exclusion criterion, as is reason to think that participation might compromise care. People who are at baseline or become ineligible due to active suicidality will be provided with support and referred back to their clinician. On a case-by-case basis, people excluded because of active suicidality may be invited to recontact researchers once treatment and symptom stability are in place.

Second, as noted above, meeting MADRS or YMRS episode criteria (> 12 and > 8, respectively) is an exclusion criterion at baseline. Following a protocol we have used previously to balance risk management with lived experience empowerment,
^
20
^ potential participants who are in an episode at baseline, but meet all other criteria for the study will be offered the option of being recontacted in 4 weeks to see if they would like to repeat the eligibility assessment (‘re-assessed’).

Third, as part of ensuring that participation does not negatively impact participants’ treatment or recovery, people showing high level of symptoms at follow-up assessment interviews (i.e., meeting episode criteria of MADRS > 12 or YMRS > 8) will be reviewed by the research team (including the study clinician) post-interview. Actions arising from this review will include sharing with the participant that they currently meet episode criteria and encouraging them to organise an appointment with their clinician. On a case-by-case basis, actions may also include, (i) offering the participant to pause their participation for 4 weeks and be recontacted to repeat the eligibility assessment, or (ii) informing the participant that they are ineligible to continue on the basis of symptom burden/complexity (this potentially difficult news would be delivered by the project manager or a clinician as required, and may include identifying other ways the individual can participate in other aspects of the team’s program of research and community outreach).

Finally, management of acute suicidality in Study 1 and Study 2 again follows principles developed in our earlier research.
^
20
^ If the CSSRS indicates active suicidality at baseline or follow-up interview, research assistants will use a warm handover procedure via teleconference to escalate the participant to a clinical psychologist (Study 1) or psychiatrist (Study 2). The clinician will then explore risk further, if necessary developing a safety plan, which may include contacting the participant’s clinician or emergency services (participants consent to this specific practice). Staff training (and an associated manual) emphasises issues of self-harm, suicidality, mania and depression symptom severity scores in this population, and use of the CSSRS interview to assess for active suicidality. Training will prioritise procedures for providing feedback in a clinically sensitive manner, and escalating risk to the on-call clinician. At all times patient welfare is prioritised over collection of data.

*Risk management Study 3*

All participants in Study 3 will be receiving active management under a specialist mental health team. Everyone receiving care under the specialist mental health services is required to have a treatment plan which includes a risk management plan. The nurse or research assistant conducting interviews will be aware of the individual’s existing treatment plan and will refer to this if required.

*Data Security*

In Study 1, data will be gathered using REDCap, a highly secure web-based research data collection system. REDCap provides several data security features, including secure passwords required for staff log-in, well-defined levels of data access based on a staff member’s role in the project, and data storage on the password-protected OneDrive of the lead organisation (Swinburne University of Technology, henceforth ‘Swinburne’). In Study 2 and 3, data will initially be collected using paper-pen and subsequently transferred to REDCap. REDCap system design will be standardised across studies where possible to facilitate merging of the data for WP4. An additional separate REDCap system will be created for the genetic and metabolomic data of Study 2.

In Study 1, video contact with participants will be conducted by Swinburne Zoom accounts or Teams accounts; participants have the option to turn off their cameras during those meetings or to request telephone interviews in place of video calls (except for the initial confirmation of identity via photo ID). In Study 2 and 3, participants will be interviewed exclusively in person. Study 3 participants who are recruited as inpatients will be interviewed in person, those recruited as outpatients will have baseline interviews in person, and follow-up interviews by phone.

Only members of the research team will have access to the data during data collection. However, deidentified data will also be released to the data safety and monitoring committee (DSMC). All data collected at each of the sites will be de-identified before transfer and uploaded as re-identifiable, password-protected files to the Swinburne OneDrive. Swinburne will hold a backup of all these data. Only members of the research team will be permitted to access these data. Data access and security arrangements will be detailed in the Participant Information Form and consented to by all participants.

A key deliverable of WP4 is a new multi-national dataset and data processing pipelines to be shared with future researchers. Data records and materials will be retained by Swinburne and archived for 20 years on Swinburne’s OneDrive. Beginning 12 months after publication, deidentified data will, on a case-by-case basis, be made available to external researchers with methodologically sound proposals that are consistent with participants’ provision of extended consent. Code for the actigraphy processing pipeline will be shared through the project’s GitHub repository server. Metabolomics data will be submitted to the Metabolights platform for sharing (
https://www.ebi.ac.uk/metabolights/index). This data repository follows globally accepted regulations.

To protect participant confidentiality, privacy standards that match or exceed those of all countries from which the project recruits will be maintained. Swinburne will be the data custodian of data from all sites. Upon completion of the project and acceptance of its primary scientific outputs, de-identified data, data analysis scripts, statistical analysis plan, informed consent, publicly available (non-copyrighted) measures will be shared on the Open Science Foundation.

